#### **11.1.1.2 Safety data set**

Safety Data Set (SS): All participants who completed treatment after randomization.

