### **3.1.4 Exclusion and dropout criteria**

- (1) Cases that do not meet the inclusion criteria and are erroneously included should be excluded.
- (2) Subjects with poor compliance who withdraw themselves during the treatment.
- (3) Cases that develop severe adverse reactions or complications, making it inappropriate to continue the treatment and thus terminating the trial.

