### **3.1.6 Case termination criteria**

(1) Subjects who experience increased pain or other severe adverse reactions during the study, making it inappropriate to continue participation.

(2) Subjects who request to withdraw from the clinical study midway.

(3) Patients who are uncooperative and non-compliant with treatment, despite repeated explanations by the clinician.

(4) Researchers should record in detail the reasons and timing of withdrawal from the study; cases that have surpassed half of the treatment duration should be included in

the efficacy analysis.

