(5) Safety Analysis: Firstly, list and describe adverse events in each group according to the relatedness requirements (including the number and incidence of various adverse events), and list their causes and explanations. If comparison is necessary,

chi-square tests may be used for statistical analysis of adverse events, summarized according to safety evaluation criteria, which are graded as follows:

1. Level 1: Safe, no adverse reactions;
2. Level 2: Relatively safe, with mild adverse reactions that do not require intervention and can continue treatment;
3. Level 3: Safety concerns, with moderate adverse reactions that can continue treatment after interventions;
4. Level 4: Study discontinued due to adverse reactions.

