#### **11.1.6 Adverse events**

All adverse events (AEs) occurring during the study must be recorded and reported, and timely and appropriate measures must be taken for participants. Researchers must inform participants to honestly report changes in their condition after treatment, avoiding leading questions. During the observation of efficacy, pay attention to adverse events. If adverse events such as fainting, pain at the acupuncture site, bleeding, hematoma, or infection occur during acupuncture, participants will receive recorded and timely proper treatment until fully recovered.

Regardless of whether adverse events are related to the treatment method of the study, they must be thoroughly recorded, including the time of occurrence, symptoms, signs, severity, duration, laboratory indicators, treatment methods and outcomes, course, follow-up time, etc., and analyze the causes of adverse events.

(1) Serious Adverse Event Determination: Serious Adverse Events (SAEs) refer to unforeseen clinical events occurring during the study period, including patient death,

life-threatening situations, resulting in hospitalization, prolonging hospital stay, long-term or significant functional impairment/disability, or requiring medical or surgical treatment to prevent serious consequences.

(2) Handling of Adverse Events: AEs occurring during the study will be summarized by total number, system organ class (SOC), or other terms, summarizing at least once occurring event incidence. AEs will also be summarized by severity and relatedness to acupuncture. SAEs leading to study discontinuation will also be summarized.

For each count and incidence, each participant is counted only once regardless of the number of occurrences. When summarizing adverse events, missing severity ratings or causality assessments will be classified as "serious" and "definitely related."

All AEs will be presented in lists, including SAEs leading to study discontinuation due to acupuncture, and events leading to fatal outcomes. Missing values and incomplete dates in the lists will be displayed consistent with original records.

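### The safety set admits only treatment completers, so participants whose session is stopped by a reaction or worsening pain fall out of the adverse-event incidences, grades and group comparison

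*Protocol*

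**What the plan says.** Section 11.1.1.2 of the protocol defines the safety population in one sentence: "All participants who completed treatment after randomization". No other section widens it.

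Two sections foresee participants who would not meet that condition. Section 3.1.4, item (3), lists among dropouts "Cases that develop severe adverse reactions or complications, making it inappropriate to continue the treatment and thus terminating the trial". Section 3.1.6, item (1), ends participation for "Subjects who experience increased pain or other severe adverse reactions during the study, making it inappropriate to continue participation".

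The safety analysis in section 11.1.5, item (5), grades safety on four levels. Levels 2 and 3 presuppose that treatment goes on; Level 3 reads "Safety concerns, with moderate adverse reactions that can continue treatment after interventions". The worst grade is "Level 4: Study discontinued due to adverse reactions".

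Section 7.2.2 calls for a statistical comparison of adverse events between the regimens. Section 11.1.6 asks for incidences that count each participant once, for a summary of serious adverse events that led to discontinuation, and for a listing of every adverse event. It also states that "missing severity ratings or causality assessments will be classified as" serious (for severity) and definitely related (for causality).

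**The concern.** Completing treatment is a post-randomisation outcome that an adverse reaction can itself prevent. Making it an entry condition for the safety set removes the participants in whom the intervention was tolerated worst, from numerator and denominator alike. What remains is a comparison between those in each arm who tolerated the session, which is not the comparison that section 7.2.2 asks for.

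The definition also sits badly with the rest of the protocol. The grading scale has a category for discontinuation, and section 11.1.6 wants events that led to discontinuation summarised, yet the population defined for safety leaves out those whose treatment was cut short. The full analysis set in section 11.1.1.1 takes in everyone randomised, so the safety population is narrower than the main efficacy population. Under section 3.1.6, item (4), a participant withdrawn after more than half of the treatment counts for efficacy, but under section 11.1.1.2 the same person does not count for safety.

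Early stopping is possible even in a single 10-minute session. Section 6 names fainting, needle-site pain, bleeding and haematoma during acupuncture. Section 4.3 has patients in acute pain bend and rotate while the needle is in place.

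**Working it through.** **1. Trace one participant through the rules.** Suppose a participant faints or has worsening pain at minute 4 and the session is stopped.

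| Protocol section | Consequence for this participant |
|---|---|
| 3.1.4 (3), 3.1.6 (1) | Dropout or terminated case |
| 11.1.1.1 | In the full analysis set |
| 11.1.1.2 | Not in the safety set, because treatment was not completed |
| 11.1.5 (5) | Would be Level 4, but is outside the set to be graded |
| 11.1.6 | Event listed, and summarised as leading to discontinuation if serious |
| 11.1.2 | Counted among discontinuations, with the reason |

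The event is therefore visible in listings and disposition tables but absent from every safety-set incidence, grade and test.

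**2. Arm size.** Section 2.2 gives a minimum of 58 per group and 8% dropout. Taking the 58 as stated, 58 / (1 − 0.08) = 63.04, rounded up to 64 per arm, and 2 × 64 = 128. This agrees with the planned total.

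**3. Expected non-completers.** 64 × 0.08 = 5.12, or about 5 per arm. If all of these fail to complete the session, the safety set holds about 64 − 5 = 59 per arm.

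**4. What the set misses.** The protocol gives no rate of stopping for adverse reactions. As an assumption, let s of the 5 non-completers per arm have stopped for that reason, with s from 1 to 5.

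| s | Share of the 64 in the arm | Of these, counted in the safety set |
|---|---|---|
| 1 | 1/64 = 1.6% | 0 |
| 3 | 3/64 = 4.7% | 0 |
| 5 | 5/64 = 7.8% | 0 |

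**5. Effect on the incidence of any adverse event.** Let m completers have at least one event, and suppose the s stopped participants are the only non-completers. The full incidence is (m + s)/64; the safety set gives m/(64 − s). The second is smaller whenever (m + s)(64 − s) > 64m, which reduces to m < 64 − s. So the arm's incidence is understated unless every completer had an event. If there are also event-free non-completers, their removal shrinks the denominator and pushes the other way, so the net error then depends on the mix.

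**6. Direction between arms.** Sections 4.2 and 4.3 say that the real needle penetrates the skin and the sham does not, so needle reactions might stop more sessions in the AA arm. But increased pain is also a reason for termination, and section 2.2 assumes a smaller fall in VAS under sham (2.7 against 4.6), so stops for pain might be commoner there. The documents do not settle which dominates.

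**The case against.** Several stronger readings are tempting, and the case against them is sound.

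*That Level 4 must be zero.* A reader might infer this from the definition. But Level 4 refers to discontinuing the study, and section 3.1.6 likewise speaks of reactions during the study. Sections 6 and 11.1.6 mention infection and haematoma and follow events to recovery, so a reaction can emerge or worsen after a completed session. Such a participant is in the safety set and can be Level 4. The route is narrow, since efficacy assessments end at 10 minutes, but it exists. The supportable statement is that Level 4 is undercounted.

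*That these events vanish.* They do not. Section 11.1.6 lists all adverse events, section 11.1.2 summarises reasons for discontinuation, and neither section 11.1.5, item (5), nor section 11.1.6 names the safety set as its population. This limits the damage to denominators, incidences, grades and tests. It does not remove the conflict: the protocol defines one safety population, and on its wording that population cannot supply the summaries requested.

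*That the comparison is biased in favour of AA.* This is plausible for needle reactions alone but is not established overall, for the reason given in step 6.

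*That intention-to-treat cures it.* Section 3.1.5 sends dropped cases to an intention-to-treat analysis, but its own note ties that to effectiveness. It does not reach safety.

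*That a blank severity field creates a false serious adverse event.* Section 11.1.6, item (1), determines serious events by their own criteria, and nothing says that an imputed severity feeds that count. The sentence is most naturally worst-case imputation with the wrong adjective.

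It is also fair that the intervention is one brief session, that few stops are likely, and that the primary efficacy analysis is untouched.

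**Conclusion.** The definition in section 11.1.1.2 should be corrected. Followed as written, it leaves out participants whose session was stopped by a reaction or increased pain, undercounts Level 4, and conflicts with the between-regimen comparison in section 7.2.2 and the grading and discontinuation summaries in sections 11.1.5 and 11.1.6.

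The size is unknown, because the protocol states no rate. On the assumption of 1 to 5 such stops among 64 per arm, 1.6% to 7.8% of an arm would be missed. This treats the 8% dropout in section 2.2 as failure to complete the session and attributes between one and all of those cases to reactions; the practical effect may be at the low end or nil. With few events expected, though, each exclusion counts.

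This should be fixed, but it does not threaten the trial: the sample size and the primary analysis are unaffected, and the underlying events are recorded. The word chosen for missing severity is a minor wording matter.

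**What to change.** Redefine the safety set in section 11.1.1.2 as all randomised participants to whom a real or sham needle was applied, analysed by the treatment actually received, whether or not treatment was completed. State in sections 7.2.2, 11.1.5 (5) and 11.1.6 that this set is the population for all adverse-event incidences, safety grades and between-group comparisons.

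As a minor wording change in section 11.1.6, classify missing severity as severe rather than serious, and say that seriousness is decided only by the criteria for serious adverse events in item (1).

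The cost is a few sentences. Sections 6 and 11.1.6 already require these events to be recorded, so no new data are needed, and neither the sample size nor the rules for ending treatment change.

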#### **11.1.2 Participant handling**

Summarize the number of participants who started, completed, and discontinued the study. Additionally, summarize the reasons for discontinuation.

#### **11.1.3 Demographics and baseline characteristics**

(1) Demographic Indicators: Age, height, and weight, etc.

(2) Basic Vital Signs: Resting heart rate, breathing, blood pressure, and body temperature, etc.

#### **11.1.4 Efficacy evaluation**

All efficacy evaluation data will be summarized separately according to the FAS and PPS sets, with the FAS set as the primary analysis method.

#### **11.1.5 Statistical analysis methods**

This study utilizes SPSS 28.0 for the analysis of clinical data. Continuous variables with normal distribution will be expressed as mean  $\pm$  SD and continuous variables with non-normal distribution will be reported as median and interquartile range (IQR).

For analyzing demographic data, continuous variables will be analyzed using the independent samples t-test or the Wilcoxon rank sum test depending on whether or not they conform to a normal distribution. Categorical variables will be analyzed using  $\chi^2$  test or Fisher's exact test. All significant demographic differences will be included as covariates in subsequent efficacy analyzes. The primary outcome indicator will be analyzed using analysis of covariance with baseline pain levels as a

covariate and group as a factor. The secondary outcomes, including changes in pain intensity at other time points (2, 5 minutes) and ROM at different time points, will be analyzed using repeated measures ANOVA or Mann-Whitney U test, depending on the data's distribution. Additionally, correlations between pain VAS scores and efficacy expectation scores will be explored using Spearman's or Pearson's correlation analysis. We will follow the intention-to-treat (ITT) principle and analyze all participants who receive treatment. Missing data of withdrawn participants will be processed using chained-equation multiple imputation.

(1) Case Distribution: Size of different data sets in each group, distribution of cases across centers, detailed list of dropouts, discontinuations, and reasons.

(2) Comparability Analysis: Compare demographic data and other baseline values to assess comparability between groups.

(3) Compliance Analysis: Compare whether patients in each group followed the design protocol. Compliance is evaluated based on the records in the participant's CRF form, calculating percentages for <80%, 80%–100%, and >100% compliance.

(4) Factors Affecting Efficacy Analysis: If there are significant differences between groups before the study or factors significantly affecting efficacy, these factors should be considered as covariates in the group comparisons, requiring covariance analysis or logistic regression, and a detailed list of concomitant medication use.

(5) Safety Analysis: Firstly, list and describe adverse events in each group according to the relatedness requirements (including the number and incidence of various adverse events), and list their causes and explanations. If comparison is necessary,

chi-square tests may be used for statistical analysis of adverse events, summarized according to safety evaluation criteria, which are graded as follows:

1. Level 1: Safe, no adverse reactions;
2. Level 2: Relatively safe, with mild adverse reactions that do not require intervention and can continue treatment;
3. Level 3: Safety concerns, with moderate adverse reactions that can continue treatment after interventions;
4. Level 4: Study discontinued due to adverse reactions.

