### **2.2 Sample size**

This study is a superiority trial designed to assess whether AA combined with active exercise is more effective than SAA combined with active exercise for the treatment of ALS. A previous study showed that VAS scores decreased by  $4.6 \pm 1.0$  and  $2.7 \pm 1.0$  after 10 minutes of acupuncture combined with exercise and sham acupuncture combined with exercise for ALS, respectively. Based on the results of this study, we predict that the change in VAS scores post-treatment will be  $4.6 \pm 1.0$  in the AA group

and  $2.7 \pm 1.0$  in the SAA group, with  $\alpha=0.025$  (unilateral),  $\beta=0.1$ ,  $\Delta=1.3$ , and  $K=1$ .

The sample size calculation is based on the following formula:

$$n_c = \frac{(Z_{1-\alpha} + Z_{1-\beta})^2 \sigma^2 \left(1 + \frac{1}{K}\right)}{(\mu_T - \mu_C - \Delta)^2}$$

It was calculated that a minimum of 58 participants were needed in each group.

Taking into account the 8 percent dropout rate, we plan to recruit at least 128 participants for this study.

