#### **5.2 Biological indicators**

(1) Demographic signs: Gender, age, height, weight, occupation, marital status, and educational background.

(2) Vital signs: Body temperature, heart rate, breathing.

(3) Basic medical history and routine physical examination.

These indicators will be recorded at the time of enrollment.

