## **5.4 Measurement indicators**

### **5.4.1 Primary outcome**

The primary outcome will be the change in pain intensity from baseline to 10 minutes after treatment as measured using VAS scores.

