### **11.1 Statistical analysis content and methods**

#### **11.1.1 Statistical analysis sets**

##### **11.1.1.1 Efficacy evaluation data set**

(1) Full Analysis Set (FAS): Includes all randomized participants. For cases not observed throughout the entire treatment process, the last observed outcome (last observation carry-forward: LOCF) is carried forward to the point of data missing. The number of participants evaluated for efficacy at the endpoint is consistent with the number at the start of the study. Comprehensive efficacy analysis is conducted using the Per Protocol Set (PPS) and the Full Analysis Set.

(2) Per Protocol Set (PPS): Includes participants who complied with the study treatment protocol, primarily those who can be measured for key indicators and have no major violations of the study protocol. Analyses of demographic and other baseline characteristics and other efficacy indicators are conducted using the PPS.

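### Beyond baseline VAS, the covariates of the primary ANCOVA are left to baseline significance tests and observed associations with outcome, so the primary model is not fixed in advance

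*Protocol*

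**What the plan says.** The primary outcome is defined in section 5.4.1: "The primary outcome will be the change in pain intensity from baseline to 10 minutes after treatment", on the VAS. Section 11.1.5 then makes three statements about the model.

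- **Named model.** "The primary outcome indicator will be analyzed using analysis of covariance with baseline pain levels as a" covariate, with group as factor. Baseline pain is therefore always in the model.
- **Rule A, mandatory.** "All significant demographic differences will be included as covariates in subsequent efficacy analyzes". The primary outcome is an efficacy analysis, so the rule reaches it.
- **Rule B, discretionary, item (4).** "If there are significant differences between groups before the study or factors significantly affecting efficacy, these factors should be considered as covariates". This repeats the baseline-difference route and adds a second one, association with efficacy, which can be known only after the outcome has been seen.

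Neither rule comes with a significance level, a closed list of candidates or an order of precedence. Nothing says that the baseline-pain ANCOVA remains primary or that extended models are sensitivity analyses.

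The candidates are listed elsewhere. Section 5.2 gives seven demographics: "Gender, age, height, weight, occupation, marital status, and educational background". Section 11.1.3 names age, height and weight and leaves the list open. Section 11.1.1.1 assigns "Analyses of demographic and other baseline characteristics" to the per-protocol set, whereas section 11.1.4 makes the full analysis set primary for efficacy.

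**The concern.** Allocation is randomised (section 2.3). A significant baseline difference is then a chance event, and its p-value says nothing about whether the variable predicts pain relief. Rule A can bring in a variable that does not matter and leave out one that does. Rule B lets the observed outcome shape the model that tests it. The two rules also differ in force: one says covariates will be included, the other that they should be considered.

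As a result, a reader of the protocol cannot write down the primary model before the data are in. At stake are the calibration of the primary test, precision that a prespecified prognostic covariate could have brought, and the trial's ability to show that the reported model was not chosen for its result. The analysis sets add to this: read together, the sections have tests in a subset defined after randomisation selecting covariates for a model fitted to everyone randomised.

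**Working it through.** **1. The plan's sample size.** Section 2.2 gives mean changes of 4.6 and 2.7, SD 1.0, margin 1.3, one-sided alpha 0.025, beta 0.1 and 1:1 allocation.

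- Difference beyond the margin: 4.6 − 2.7 − 1.3 = 0.6, which is 0.6 SD.
- n per arm = 2 × (1.960 + 1.282)² / 0.6² = 58.37. The plan states 58; rounding up would give 59. Power at 58 is 89.8% by the normal formula and 89.3% by the t distribution.
- 58 / 0.92 = 63.04, so 64 per arm and 128 in total, as stated.

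The checks below use 58 per arm and 0.6 SD.

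**2. How often chance alone changes the model under Rule A.** Assume independent tests at two-sided 0.05, a level the protocol does not give. P(at least one significant) = 1 − 0.95^k.

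| Candidates | k | Probability |
|---|---|---|
| Named in section 11.1.3 | 3 | 1 − 0.857 = 14% |
| Listed in section 5.2 | 7 | 1 − 0.698 = 30% |

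**3. Rule A applied mechanically, one candidate.** Simulation with baseline VAS always in the model, two-sided nominal 5% (equivalent to one-sided 0.025 in each direction). The correlation of the covariate with the outcome is assumed.

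| Correlation | Type I error, Rule A | Power, Rule A | Power, covariate always in | Power, covariate never in |
|---|---|---|---|---|
| 0.3 | 4.9% | 89% | 91% | 89% |
| 0.5 | 4.3% | 90% | 95% | 89% |
| 0.7 | 3.7% | 91% | 99.5% | 90% |

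The figures are subject to simulation error of a few tenths of a point for type I error and up to about a point for power.

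**4. Both rules, ten candidates.** The ten are the seven demographics and the three vital signs in section 5.2; vital signs could enter only through item (4). Assumptions: independent candidates, baseline pain explaining 25% of the variance, and one candidate truly prognostic with R² of 0, 0.1, 0.3 or 0.5. The test is one-sided at 0.025, with 40,000 null trials and 10,000 trials at 0.6 SD. Power is higher than in step 3 because baseline pain explains variance here.

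| Model | Type I error at R² 0 / 0.1 / 0.3 / 0.5 | Power (%) |
|---|---|---|
| Baseline pain only | 0.0243 / 0.0248 / 0.0249 / 0.0247 | 95.8 / 95.6 / 95.9 / 95.5 |
| Plus prespecified prognostic covariate | 0.0244 / 0.0250 / 0.0254 / 0.0247 | 95.6 / 97.3 / 99.8 / 100 |
| Selected by baseline test | 0.0246 / 0.0230 / 0.0203 / 0.0144 | 95.4 / 95.4 / 96.4 / 96.9 |
| Selected by baseline test or association with outcome | 0.0249 / 0.0253 / 0.0258 / 0.0244 | 95.1 / 97.0 / 99.6 / 100 |
| Most favourable of baseline-only and the two selected models | 0.0286 / 0.0354 / 0.0413 / 0.0448 | not the point here |

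Baseline-test selection is at or below nominal throughout. Selection that also uses the outcome stays close to nominal. Only free choice among the models goes clearly above it.

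**The case against.** The best defence is that the plan already fixes the covariate most directly tied to the outcome, that Rule A is mandatory and so leaves no choice, and that the statistical analysts are blinded (section 2.4). Item (4) sits under its own heading and mentions logistic regression, which does not fit a continuous VAS change, so it can be read as generic supportive analysis. Much of this stands, and it rules out three stronger readings that a reader might infer.

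- **That no covariate enters without a significant test.** The text does not say so: baseline pain is always included.
- **That the rules inflate the false-positive rate.** Applied mechanically they do not. Baseline-test selection is conservative, and selection that adds the outcome route stays near nominal.
- **That Rule A costs power against the plan's own ANCOVA.** It does not, to any material degree: in step 4 the difference runs from −0.4 to +1.3 points. The loss exists only against a prespecified prognostic covariate, and its size depends on correlations the protocol does not give. If the test is against zero instead of the 1.3 margin, the planned effect is 1.9 SD and power is close to 100% whichever model is used.

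The 14% and 30% are also soft. Gender, height and weight are correlated, and a chance imbalance in a non-prognostic variable barely matters (type I error 0.0246 and power 95.4% against 95.8% at R² = 0).

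What the defence does not meet is the missing hierarchy. Rule A says all efficacy analyses, item (4) speaks of the group comparisons, and neither yields to the named ANCOVA. Blinding limits steering towards one arm but does not fix the model. Nor is this detail that can simply be left to an analysis plan: one that named a closed covariate list would have to contradict the protocol's stated rule.

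**Conclusion.** The point holds as a prespecification defect. Baseline VAS is fixed; everything else in the primary model depends on chance imbalance or on the observed outcome. By chance alone the model would change in about 14% to 30% of trials, assuming independent tests at 0.05 and three to seven candidates. With a prognostic covariate, the baseline-test rule brings a nominal 5% test down to about 4.9%, 4.3% or 3.7%, and gives up roughly 2, 5 and 8 points of power against prespecifying that covariate (91 − 89, 95 − 90, 99.5 − 91 = 8.5), at assumed correlations of 0.3, 0.5 and 0.7.

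A one-sided error of 0.029 to 0.045 against 0.025 would require the most favourable model to be picked. Item (4)'s wording leaves room for that, but the documents give no ground to say it is intended. The split between the per-protocol set for baseline comparisons and the full analysis set for efficacy is real; its effect has not been quantified. This should be corrected, but it does not by itself invalidate the design.

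**What to change.** In section 11.1.5, delete the sentence on significant demographic differences and the covariate clause in item (4). State the primary model as change in VAS = group + baseline VAS, plus any further covariates named now on prognostic grounds and kept whatever imbalance is observed. Age and symptom duration are possible examples; section 5.1 already has both recorded. Label any other adjusted model as a sensitivity analysis. Present baseline data descriptively for the full analysis set, and amend section 11.1.1.1 to match.

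The cost is wording only: no new data and no change to the sample size. A named covariate that proves non-prognostic costs one degree of freedom. Fixing the model at group plus baseline VAS alone secures prespecification and calibration but brings no power gain over the present rule; that gain comes only from naming a covariate that is truly prognostic.

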#### 3.1.2 Inclusion criteria

1. Meet the diagnostic criteria for ALS;

2. Unilateral low back pain, age 18-60 years;
3. Duration of the disease  $\leq 3$  days;
4. Moderate to severe pain, with the visual analogue score (VAS) between 4 and 8;
5. Signed the informed consent form.

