### **5.4.2 Secondary outcomes**

(1) Changes in pain intensity at 2 and 5 minutes after treatment will also be measured using VAS scores.

(2) Lumbar range of motion (ROM) will be assessed at baseline, 2, 5, and 10 minutes during treatment. Participants will be instructed to stand with their feet slightly apart, shoulder width apart, and their body relaxed. Measurements will be taken for forward flexion, backward extension, right lateral flexion, and left lateral flexion in order.

(3) Patient expectations of treatment outcomes will be assessed at baseline using the efficacy expectations scale.

(4) The success of the blinding will be assessed at the end of treatment using a blinded questionnaire.

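### Secondary VAS and ROM outcomes go to RM-ANOVA or Mann-Whitney according to the observed distribution, with no prespecified baseline covariate; lateral flexion is defined by anatomical side in one-sided pain

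*Protocol*

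**What the plan says.** **Primary outcome.** Protocol section 11.1.5 says that it "will be analyzed using analysis of covariance with baseline pain levels as a" covariate, with group as a factor.

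**Secondary outcomes.** The same paragraph says that VAS change at 2 and 5 minutes and ROM at the different times "will be analyzed using repeated measures ANOVA or Mann-Whitney U test, depending on" the distribution of the data. It does not say how the distribution is to be judged, and it names no covariate.

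**Conditional covariates.** Two rules in section 11.1.5 can bring covariates in. Demographic variables enter if they differ significantly between groups. Under item (4), pre-study differences that are significant, or factors found to affect efficacy, are to be considered as covariates.

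**Laterality.** Section 3.1.2 admits only "Unilateral low back pain, age 18-60 years". Section 4.3 places the needle on the healthy side. Section 5.4.2 measures forward flexion, backward extension, "right lateral flexion, and left lateral flexion in order", and the table in section 8.2 has one column for each anatomical side. No section re-expresses these relative to the painful side.

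**The concern.** Three features of the secondary analysis deserve attention.

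1. **The switch.** Repeated measures ANOVA compares group means and their course over time. Mann-Whitney U compares ranks between two groups at a single time, with no time or group-by-time term. If the data decide between them, they also decide the question asked.
2. **Baseline.** VAS and ROM are both measured at baseline, yet only the primary analysis is certain to model the baseline value. A covariate rule triggered by significance gives no assurance of adjustment and is itself driven by the data.
3. **Sides.** If participants with left-sided and right-sided pain are averaged within one column for right flexion, that mean mixes bending toward the pain with bending away from it.

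ROM is the only mobility outcome, and section 1 gives limited efficacy on mobility as background to combining auricular acupuncture with exercise. A less precise analysis there could leave a real effect unclear.

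**Working it through.** **The Protocol's own figure (section 2.2).** The inputs are "VAS scores decreased by $4.6 \pm 1.0$ and $2.7 \pm 1.0$ after 10 minutes", a margin of 1.3, one-sided alpha 0.025, power 90% and equal allocation.

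n = (1.960 + 1.282)² × 1.0² × 2 / (4.6 − 2.7 − 1.3)² = 58.37 per group

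The Protocol states that "a minimum of 58 participants were needed in each group"; strict rounding up gives 59. With 8% dropout, 58 / 0.92 = 63.04, so 64 per group and 128 in total, as stated. This concerns the primary outcome only. No effect, SD or power is given for ROM, so the figures below rest on assumptions, shown over a range.

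**Precision lost without baseline in the model.** Let ρ be the correlation of baseline with the post-treatment value, with equal SDs. At one time point the variances are proportional to 1 (post score), 2(1 − ρ) (change score) and 1 − ρ² (ANCOVA). The ratios to ANCOVA are 2/(1 + ρ) for change and 1/(1 − ρ²) for post. Both exceed 1 whenever ρ lies between 0 and 1.

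| ρ | Change / ANCOVA | Post / ANCOVA |
|---|---|---|
| 0.3 | 1.54 | 1.10 |
| 0.5 | 1.33 | 1.33 |
| 0.7 | 1.18 | 1.96 |

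For the average of three post-treatment times with equal correlations, put m = (1 + 2ρ)/3. The variances are m (post), m + 1 − 2ρ (change) and m − ρ² (ANCOVA). The ratios are 2.11, 1.60 and 1.29 for change, and 1.20, 1.60 and 2.58 for post.

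**In terms of power.** With 58 per arm and two-sided 0.05, power = Φ(d / (k√(2/58)) − 1.96), where d is the assumed effect in SDs of the post score and k² is the relevant variance above. For Mann-Whitney on the change score, the first term is multiplied by √(3/π).

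| d | ρ | Post | Change | Mann-Whitney on change | ANCOVA |
|---|---|---|---|---|---|
| 0.4 | 0.3 | 58% | 45% | 43% | 62% |
| 0.4 | 0.5 | 58% | 58% | 56% | 70% |
| 0.4 | 0.7 | 58% | 79% | 78% | 86% |
| 0.5 | 0.3 | 77% | 62% | 60% | 81% |
| 0.5 | 0.5 | 77% | 77% | 75% | 88% |
| 0.5 | 0.7 | 77% | 94% | 93% | 97% |

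Under normality the rank test costs only 1 − 3/π = 4.5% in efficiency. The loss comes from not modelling baseline.

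**VAS separately.** Section 2.2 expects a difference of 4.6 − 2.7 = 1.9 with SD 1.0, that is 1.9 SD of the change score at 10 minutes. If the early effect were only a third of this (0.63 SD of change), 0.63 / √(2/58) − 1.96 = 1.43 to 1.45 (by rounding). Power on the unadjusted change score, against no difference, is about 92%, and about 91% for Mann-Whitney.

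**Lateral flexion.** Suppose half the participants have pain on each side, the effect is D in the more responsive direction relative to the pain, and fD in the other. Each anatomical column then shows D(0.5 + 0.5f), and the sample needed grows by 1/(0.5 + 0.5f)².

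| f | Effect shown | Sample multiplier | Simulated ANCOVA power, left column |
|---|---|---|---|
| 0 | 0.50 D | 4.0 | 33% |
| 0.5 | 0.75 D | 1.78 | 63% |
| 1 | 1.00 D | 1.0 | 84% |

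The simulation (2,000 runs per row) took D = 0.5 SD, ρ = 0.5 and a baseline deficit of 1 SD on the painful side. Analysing the painful-side direction gave 87 to 88% in all three rows.

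**The case against.** The strongest reply is that the plan uses more baseline information than a quick reading suggests, and much of it stands.

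- A reader might infer that the secondary analyses ignore baseline. For VAS they do not: the outcome is a change, so even Mann-Whitney would use baseline by subtraction. ROM is measured at 0, 2, 5 and 10 minutes; if time 0 is a level in the repeated measures ANOVA, the group-by-time term reflects change from baseline. Item (4) of section 11.1.5 could also admit baseline as a covariate. What is missing is a commitment to model it, not every use of it.
- A reader might infer that the early VAS results would be underpowered, or not comparable with the 10-minute result. Section 2.2's expected effect argues against the first. On the second, change-score analysis and ANCOVA estimate the same mean difference under randomisation and differ only in precision; comparability fails only if the rank test is used.
- A reader might infer that right/left coding halves the effect. Halving is the worst case. No section says the response is confined to one direction, section 4.3 exercises all directions, and sections 5.4.2 and 8.2 describe measurement and recording. No text commits the analysis to pooling by anatomical side.
- Some of this detail could properly sit in a statistical analysis plan, which is not at hand. That does not dispose of the first point, because section 11.1.5 itself fixes the data-driven switch.

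**Conclusion.** The point holds in limited form, for secondary outcomes only.

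Section 11.1.5 lets the observed distribution choose between two tests that answer different questions, with no stated criterion, and does not prespecify baseline adjustment for these outcomes as it does for the primary. Over assumed correlations of 0.3 to 0.7, the variance penalty at one time point is 1.18 to 1.54 for change scores and 1.10 to 1.96 for post scores. Mann-Whitney itself adds little loss. VAS power is probably adequate either way, so the benefit lies mainly with ROM, where the Protocol gives no effect, SD or correlation and the true size is unknown.

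The laterality point is conditional. If lateral flexion is analysed as right and left, dilution ranges from nothing (both directions respond equally) to about half (only one responds, with half of participants painful on each side). Forward flexion and backward extension are unaffected. The primary ANCOVA and N = 128 stand.

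**What to change.** 1. In section 11.1.5, replace the distribution-driven choice with one prespecified longitudinal model for VAS and for each ROM direction: a mixed model or ANCOVA with group, time, group-by-time and the baseline value of the same measure, and group contrasts at each time. Keep a rank-based analysis as sensitivity only. Include baseline whether or not the groups differ significantly on it.
2. Record the painful side on the CRF. It is known when the needle is placed, but sections 5.1 to 5.3 do not list it as a recorded item. In sections 5.4.2 and 11.1.5, define the analysed lateral flexion variables as toward and away from the painful side; measurement can stay as it is.

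The cost is a change of wording, one CRF item, a simple recode and slightly more analysis work. No extra participants or assessments are needed.
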